### 4.3.2. Analysis Plan

#### 4.3.2.1. Comparison of patient-level outcomes (HRQoL and Symptom distress) - Specific Aim 1

The effect of the intervention on child quality of life and symptom burden outcomes (see section 2.4) will be estimated using mixed linear models, with patient as a random effect and group, time (categorical) and group x time interaction and the stratification factors as fixed effects. . The same analysis will be undertaken for the respective domain subscales of PedsQL (physical and psychosocial) and PQ-MSAS (physical and psychological).

#### 4.3.2.2. Comparison of parent-level outcomes (anxiety, depression, HRQoL, and burden) - Specific Aim 2

The same analytical approach described for patient-level outcomes will be followed to analyze parent S-TAI-State, CES-D-10 mean scores and aRSQ symptom-related scores. In S-TAI-State analysis, we will additionally adjust by baseline S-TAI-Trait score. We will also compare depression (CES-D-10  $\geq 10$ ) over time between the two groups using generalized linear mixed models with logit link and binomial distribution. As gender is a predictor of these outcomes, it will be included in these models if imbalanced between arms.

#### 4.3.2.3. Comparison of family activation outcomes - Specific Aim 3

Mixed models, similar to those described for patient-level outcomes, will be fitted to estimate the effect of the intervention on change between week 16 and baseline in Brief COPE active coping, planning, and instrumental support Scores, Total No. of, and No. of different, complementary therapies, and No. of psychosocial clinician encounters over the 16-w study period. Link and distribution for these models will be defined based on the distribution of the outcome variable. We will explore whether change in parent's activation score is modified by parent/child characteristics (e.g. parent's gender, S-TAI-Trait, CES-D-10 scores; and child's diagnosis, among others) including the corresponding interaction terms.

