### 1.3.1. Design Rationale

Because we are testing a model of care, the study is designed with a strong pragmatic emphasis. We use existing PC clinicians to deliver the intervention, do not require extra visits, and have chosen outcomes that are highly relevant to participants. We expect that this pragmatic design will contribute to understanding how to integrate pediatric PC services in real life settings.

We opted for individual randomization as the best strategy, even though there is risk for contamination. Potential sources of contamination include: oncology clinicians having patients in both arms and subsequently becoming “activated,” PC response teams becoming better “activators” and thus changing the way they intervene with “usual care” group referrals, or, patients and families “activating” other families. Based on our prior RCT and formative work, we estimate these risks are small. At any given time, most oncology providers will have 1-2 patients on study and these providers are not specifically targeted in this intervention (they will be informed about study procedures but will not receive specific training); neither oncology providers nor PC Response team will receive PediQUEST reports of patients in the “usual cancer care” group, and, patient-to-patient activation was not an issue during the pilot. For these reasons we believe that the possibility of contamination is limited. Further, alternatives are not practicable. Oncologist-level randomization results in the same risks because patients are usually seen by more than one oncologist (and given our outcomes are at the patient level we preferred this alternative). A cluster trial may be the ideal design, but it would necessarily involve a large number of sites significantly increasing the cost/benefit ratio.

An additional limitation of the study is the relatively small sample size, mostly determined by the small size of the target population, which despite randomization, carries the risk for imbalance of prognostic factors between arms. To minimize this risk, we will perform a stratified randomization.

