The 2-week run-in period is established to identify and exclude non-responder dyads before randomization to decrease the frequency of missing data for the primary outcome. Non-responders are defined as those who of the three PQ-Surveys assigned during the run-in period have <2 answered. PediQUEST-Surveys will be considered answered if the survey could be scored, i.e. a survey with >50% of the questions answered. Both patient and parent must be responders for the dyad to continue. Pilot data showed that participants who did not register in the PediQUEST web system did not differ from those in the responder group in terms of diagnosis, age, or survival. The 16-week follow-up period was defined for practical reasons. From our prior work we know that (a) short enrollment periods, enhance recruitment and retention; and (b) intermittent attrition increases

[figure not shown]

over time, especially after 20 weeks. Considering the intra-subject variability of HRQoL scores over time, we chose a 16-week period to allow for a more precise measure of the main outcome while aiming to improve enrollment and intermittent attrition. In addition, pilot data showed the need to allow enough time for intervention effects to be demonstrated (for example a preventive measure only takes effect when the next treatment cycle begins) making shorter follow-up less advisable. Finally, the 16-week period also poses an acceptable burden on PC teams whose workload will be increased without a corresponding increase in staff.

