| PediQUEST Survey (weekly, from week -2 to week 16)                                                                                                                                                                                                                                                                                     |                                                                                                                                  |       |       |                                                                                                                                                         |     |      |     |             |      |     |                                                                                                              |             |
|----------------------------------------------------------------------------------------------------------------------------------------------------------------------------------------------------------------------------------------------------------------------------------------------------------------------------------------|----------------------------------------------------------------------------------------------------------------------------------|-------|-------|---------------------------------------------------------------------------------------------------------------------------------------------------------|-----|------|-----|-------------|------|-----|--------------------------------------------------------------------------------------------------------------|-------------|
| For these aims we will use the English and Spanish PQ-Surveys which have 5 versions (respondent- and age-adapted) that collect both parent and child reports (child from the age of five). * Children will answer the same survey version throughout the 18 weeks according to the age at time of enrollment. |                                                                                                                                  |       |       |                                                                                                                                                         |     |      |     |             |      |     |                                                                                                              |             |

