### 2.6.1. Power considerations

Although the SS is mainly driven by pragmatic considerations (target population is small), power calculations were conducted and indicate that our projected minimal SS of 68 children per group provide sufficient power for both primary and secondary outcomes for clinically meaningful effect sizes. All power calculations presented below were computed with two sample independent one-side tests,  $\alpha=0.05$  unless otherwise specified. For Aims 1 and 2 power estimates are conservative because they only use one observation per subject (average across time) without accounting for the repeated measures within subject.

*Aim 1 HRQoL (primary) and Symptom (secondary) outcomes:* Standard deviations for these outcomes were estimated using data from our PQ study (39 weeks follow up, surveys answered when attending clinic or once a month). For each child, we identified all 16-w periods with  $\geq 6$  surveys and calculated mean PedsQL total and mean PQ-MSAS total scores for each 16-w period. We randomly selected one period per child and estimated the standard deviation of 16-week PedsQL means (SD). Strategy was repeated 10 times and a pooled estimate was calculated. A sample size of 136 children (68 per group) achieves 85% power to detect a 4.4 point increase (MCID) in the mean over 16-w PedsQL Total score (SD for both groups 9.5), and a 95% power to detect a 3-point decrease in mean over 16-w PQ-MSAS total score (SD = 5.3). These power calculations are conservative as they are based on mixed responses coming from parents and children, while in the current proposal responses from different informants will be considered in separate analyses and are expected to have less variability.

*Aim 2 Parental anxiety (S-TAI-State), and depression (CES-D-10) (secondary outcomes):* A sample size of 68 parents per group achieves more than 80% power to detect a moderate to large effect size (Cohen's  $d = 0.43$ ). For example, this effect size would correspond to a difference of 5.2 points in mean S-TAI-State (SD=12.2).

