## 4.3. Statistical methods

### 4.3.1. Overview

All statistical analysis will be conducted on an intention-to-treat basis, i.e. all randomized participants with baseline and at least one post-baseline measurement will be analyzed by original treatment assignment, regardless of adherence. Baseline characteristics will be described and compared between groups using summary measures (e.g. means, medians, rates) and tests selected based on variable distribution. Analyses will be adjusted for factors used in the stratified randomization (center, age group and type of cancer). In addition, if, despite efforts to standardize intervention delivery (section 5.1), we identify substantial differences in fidelity across sites, we will evaluate effect modification by site including the site  $\times$  intervention interaction in the models. The False Discovery Rate criterion will be used to correct for multiple testing in non-planned analyses. Co-I [name] has been the primary biostatistician for all prior PQ analyses and is best suited to head the PQ Response's analysis, along with her team at Deakin University. The PI and Co-I [name] will be part of the leadership team. While all Co-Is will be involved in analysis and manuscript writing, some may take a more prominent role according to their specific expertise (e.g. [name], [name] with aim 2, and [name] with aim 3). DFCI will coordinate data cleaning and programming.

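### The primary PedsQL model, and the PQ-MSAS model that shares it, make no covariate use of the pre-randomisation scores collected in the run-in, which costs precision and protection against chance imbalance but not validity

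*Protocol*

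**What the plan says.** Section 4.3.2.1 gives the model for child quality of life and symptom burden term by term: a mixed linear model "with patient as a random effect and group, time (categorical) and group x time interaction and the stratification factors as fixed effects". Section 4.3.1 is consistent with this: "Analyses will be adjusted for factors used in the stratified randomization (center, age group and type of cancer".

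The pre-randomisation scores are collected. Table 3 in Section 2.5.1 heads the relevant block "PediQUEST Survey (weekly, from week -2 to week 16", and that survey contains both PedsQL and PQ-MSAS. Section 1.3.1 makes answering it the condition for randomisation: "Non-responders are defined as those who of the three PQ-Surveys assigned during the run-in period have <2 answered". The analysis set in Section 4.3.1 also calls for a baseline value: "all randomized participants with baseline and at least one post-baseline measurement will be analyzed by original treatment assignment".

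Section 1.3.1 concedes that the small sample "carries the risk for imbalance of prognostic factors between arms" and answers with stratified randomisation. The strata in Section 3.1 are centre, age group and haematological versus other cancer; none is baseline quality of life.

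For one parent outcome the protocol does name a baseline covariate: "In S-TAI-State analysis, we will additionally adjust by baseline S-TAI-Trait score".

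**The concern.** The primary outcome (Section 2.4.1) is the between-arm difference in the mean PedsQL total over 16 weeks. A child's own score just before randomisation is normally informative about that mean, and here it is averaged over two or three weekly surveys. If it stays out of the model, the between-child variance that it explains remains in the standard error, and part of any chance difference in starting quality of life passes into the estimate.

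This matters more than usual here, because Section 2.6.1 says that the sample size was set mainly by the small target population. Precision cannot readily be bought with more patients.

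The omission looks like a stated specification rather than a detail left for later. The terms are listed, and the next subsection adds S-TAI-Trait explicitly where a baseline covariate is wanted.

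**Working it through.** **Inputs.** From Section 2.6.1: 68 per arm, difference 4.4 points, SD of the 16-week mean 9.5 in both arms, one-sided α = 0.05 ("All power calculations presented below were computed with two sample independent one-side tests"), one average per child, no baseline adjustment. Assumed: r, the correlation between the run-in mean and the 16-week mean, from 0.3 to 0.7. The documents give no value.

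**1. The protocol's figure.** SE = 9.5 × √(2/68) = 1.63, so the noncentrality is 4.4/1.63 = 2.70. With 134 degrees of freedom, the noncentral t gives 85.1% one-sided, which reproduces the stated 85%. The same inputs two-sided give 76.5%.

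**2. With baseline as a covariate.** The residual SD is 9.5 × √(1 − r²), the variance falls by r², and the unadjusted design of equal precision has 68/(1 − r²) per arm.

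| r | Residual SD | SE | Variance reduction | Power, one-sided | Power, two-sided | Equivalent n per arm |
|---|---|---|---|---|---|---|
| 0 | 9.5 | 1.63 | 0% | 85% | 76% | 68 |
| 0.3 | 9.1 | 1.55 | 9% | 88% | 80% | 75 |
| 0.5 | 8.2 | 1.41 | 25% | 93% | 87% | 91 |
| 0.6 | 7.6 | 1.30 | 36% | 96% | 92% | 106 |
| 0.7 | 6.8 | 1.16 | 49% | 98% | 96% | 133 |

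**3. Is that range of r reasonable?** Under the protocol's own random patient effect (equal correlation between any two weeks), with ICC denoting the correlation between two single scores, the mean of k run-in scores and the mean of 16 weekly scores correlate

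r = ICC / √{[ICC + (1 − ICC)/k] × [ICC + (1 − ICC)/16]}.

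For ICC = 0.2, 0.3 and 0.5 this gives 0.59, 0.70 and 0.84 with k = 3, and 0.52, 0.63 and 0.79 with k = 2. If correlation decays over time, r is lower: 0.32 to 0.71 in the patterns tried. The low end therefore cannot be excluded.

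**4. Effect of chance imbalance.** The SE of the between-arm baseline difference is √(2/68) = 0.17 SD. An imbalance of one SE moves the unadjusted estimate by r × 0.1715 × 9.5:

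- r = 0.3: 0.5 points (11% of 4.4)
- r = 0.5: 0.8 points (19%)
- r = 0.7: 1.1 points (26%)

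**5. Could baseline already be in the model as a level of time?** Section 4.3.2.1 does not say whether the run-in weeks are levels of the categorical time factor. If they are, a free group-by-time interaction estimates each arm's baseline mean separately, and with complete data the post-randomisation contrast gains nothing. As a check, take equal correlation, ICC = 0.5, one baseline score, and units of single-score variance:

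- Per-child variance of the 16-week mean, free interaction: 0.5 + 0.5/16 = 0.531.
- With that baseline as a covariate, or with baseline means constrained equal: 0.531 − 0.5² = 0.281.

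The precision is recovered only by conditioning on baseline or by constraining it.

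**The case against.** The strongest reply is that nothing here is an error. In a randomised comparison, leaving out a prognostic covariate of a linear model neither biases the treatment effect nor inflates the type I error. The power was computed without baseline, reproduces, and is described in Section 2.6.1 as conservative. All of that stands, and it is why this is an efficiency point.

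The size is also uncertain. With no r in the documents, the gain may be modest: at r = 0.3, about three percentage points of one-sided power. That stands too. A reader might infer that a large gain is assured; the documents do not support that.

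The analysis set's requirement for a baseline suggests that baseline is meant to be used somehow. This is fair, but the only use the listed terms leave open is as a level of time, and step 5 shows that this does not help the 16-week mean.

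Three further inferences should be resisted:

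- **The trial is underpowered at 76%.** That figure comes from switching to a two-sided test, which is a separate matter from the missing covariate.
- **All of a baseline imbalance reaches the estimate.** Only the correlated part does, and the model already adjusts for the strata.
- **Every randomised dyad has a usable baseline from both informants.** Section 2.3.1 allows rare randomisation of dyads that miss the responder rule. Section 3.1 counts answered surveys regardless of which member of the dyad answered, whereas Section 1.3.1 requires both to respond. Section 2.5 has no self-report at ages 2-4.

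Extending the point to the parent outcomes needs care. S-TAI-State and CES-D-10 are not in the week -2 packet. Section 2.5 starts them at randomisation, and Section 3.2 says that the trial is unblinded from then on. A week-0 answer may follow knowledge of the allocation. Using the earlier S-TAI-Trait score is therefore a defensible choice.

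**Conclusion.** The point holds as a recommended improvement. The listed PedsQL and PQ-MSAS models make no covariate use of scores that the run-in collects for nearly all dyads, and reading baseline as a level of time does not repair this. The comparison remains unbiased and the stated 85% power remains correct.

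The loss in variance is r²: 9% at r = 0.3, 25% at 0.5 and 49% at 0.7. These figures rest on an assumed r, on the protocol's SD of 9.5, and on the simple two-sample calculation, which ignores what the stratification factors explain. If those factors already account for part of the baseline, r should be read as the correlation that remains after them. The PQ-MSAS gain was not calculated separately; the structure is the same.

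**What to change.** Before any unblinded analysis, amend Section 4.3.2.1 as follows.

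1. For PedsQL and PQ-MSAS, add as a fixed covariate the mean of the same informant's available run-in scores. Alternatively, use a constrained longitudinal model with a common baseline mean in the two arms. The second option can keep children whose own baseline is missing, provided that the baseline requirement in Section 4.3.1 is relaxed to match.
2. State that the treatment effect is the group contrast averaged over post-randomisation weeks 1-16, with run-in weeks excluded from that average.
3. Adjust S-TAI-State and CES-D-10 for week-0 scores only where these were completed before the allocation was disclosed. Apply the same check to any week-0 PediQUEST survey used as baseline.

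The cost is a short amendment and no new data. The protocol is at version 17.1 of April 2022, first enrolment was in April 2018, and Section 5.1.3 schedules interim looks at the primary endpoint at months 12 and 24. The amendment should therefore be dated, give its reason, and record that it was made without sight of results by arm.

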|                                                                     | Social Support              | Medical Outcomes Study Social Support-Short Form                                                                             | 4 domains: emotional/ informational, tangible, affectionate, and positive social interaction; 8-items. High reliability ( $\alpha > 0.91$ ) and stability over time.                                                                                                                                                                                                                                                                                                                                                                                                                                                                               |
|                                                                     | Anxiety                     | Spielberger's State-Trait Anxiety Scale (S-TAI)-Trait subset                                                                 | Measures trait anxiety (20 items); evaluates relatively stable aspects such as calmness, confidence, and security. Response options: frequency of feelings "in general:" 1) almost never, 2) sometimes, 3) often, and 4) almost always. Scoring: Item scores are added. Scoring is reversed for anxiety-absent items. Range of scores for S-TAI-Trait is 20–80 (higher indicates greater anxiety). Validity and reliability are high. High stability over time.                                                                                                                                                                      |

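### The parent-depression (CES-D-10) models name no baseline parent-distress covariate although two are collected: a cheap gain in efficiency, not an error

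*Protocol*

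**What the plan says.** Protocol section 4.3.2.2 carries the patient-level model over to the parent scores: "The same analytical approach described for patient-level outcomes will be followed to analyze parent S-TAI-State, CES-D-10 mean scores and aRSQ symptom-related scores". Section 4.3.2.1 defines that model as a linear mixed model "with patient as a random effect and group, time (categorical) and group x time interaction and the stratification factors as fixed effects". CES-D-10 of 10 or more is compared "over time between the two groups using generalized linear mixed models with logit link and binomial distribution".

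Two further covariates are named for the parent outcomes. One applies to state anxiety alone: "In S-TAI-State analysis, we will additionally adjust by baseline S-TAI-Trait score". The other is parent gender: "it will be included in these models if imbalanced between arms".

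Table 3 (section 2.5.1) puts S-TAI-Trait in the Baseline Packet at week -2, before randomisation, and says of it "Validity and reliability are high. High stability over time". The same table has S-TAI-State and CES-D-10 in the monthly parent questionnaires at weeks 0, 4, 8, 12 and 16. Section 4.3.1 limits the analysis set to participants who have a baseline and at least one later measurement. No section says whether a week-0 score is modelled as a response or as a covariate.

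**The concern.** Depression is one of the outcomes named in hypothesis H2 (section 1.2.2). The stratification factors in section 3.1 are centre, child age group and type of cancer, and none of them measures the parent's own distress. Section 1.3.1 admits that a small sample risks imbalance in prognostic factors and relies on stratification against it, but these strata cannot balance parental distress.

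The protocol treats S-TAI-Trait as relevant beyond state anxiety. It is a possible modifier of activation change in section 4.3.2.3 and an example of a confounder in the mediation analysis in section 4.3.2.4. Yet neither depression model names it, or any other baseline distress score. If Trait predicts CES-D-10, the continuous comparison has a larger residual variance than the collected data require.

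**Working it through.** **Inputs.** From section 2.6.1: 68 parents per arm, d = 0.43, one-sided alpha 0.05, one averaged observation per parent, no covariate. The protocol gives no correlation (rho) between Trait and CES-D-10, so every rho below is an assumption.

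**Step 1: the plan's own figure.** Power = Φ(d × √(n/2) − 1.645) = Φ(0.43 × √34 − 1.645) = Φ(2.507 − 1.645) = 0.806. The exact noncentral t gives 0.802. The protocol's example of 5.2 points with SD 12.2 gives 0.800. A two-sided test gives 0.708, so the stated figure is the one-sided one, and it needs no covariate.

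**Step 2: continuous CES-D-10, Trait as the only covariate.** The residual SD is multiplied by √(1 − rho²), so power = Φ(2.507/√(1 − rho²) − 1.645).

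| Assumed rho | Variance removed (rho²) | One-sided power |
|---|---|---|
| 0 | 0% | 0.806 |
| 0.2 | 4% | 0.820 |
| 0.3 | 9% | 0.837 |
| 0.4 | 16% | 0.862 |
| 0.5 | 25% | 0.894 |
| 0.6 | 36% | 0.932 |

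**Step 3: what Trait adds once week-0 CES-D-10 is a covariate.** Let b be the correlation of week-0 with follow-up CES-D-10, t that of Trait with follow-up, and c that of Trait with week 0. Then R² = (b² + t² − 2btc)/(1 − c²), and power follows as in step 2 with R² in place of rho². The grid is b from 0.5 to 0.7, t from 0.3 to 0.6 and c from 0.4 to 0.7, all assumed.

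- Least gain, for example b = 0.5, t = 0.3, c = 0.6: R² = (0.25 + 0.09 − 0.18)/0.64 = 0.25. This equals b², so Trait adds nothing and power stays at 0.894.
- Greatest gain, b = 0.5, t = 0.6, c = 0.4: R² = (0.25 + 0.36 − 0.24)/0.84 = 0.440. Power rises from 0.894 to 0.956.

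Over the grid Trait adds about 0 to 0.19 to R² and about 0 to 6 power points. Week-0 CES-D-10 alone gives 0.894, 0.932 and 0.969 at b = 0.5, 0.6 and 0.7.

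**Step 4: CES-D-10 ≥ 10.** This is a simulation of a logistic model at a single time point: 68 per arm, 3000 runs per rho, a normal latent score shifted by 0.43, and a cut 0.2 SD above the control mean (assumed).

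| Assumed rho | Log odds ratio, unadjusted → adjusted | SE, unadjusted → adjusted | Power, unadjusted → adjusted |
|---|---|---|---|
| 0.3 | −0.72 → −0.76 | 0.37 → 0.39 | 0.61 → 0.63 |
| 0.5 | −0.73 → −0.87 | 0.37 → 0.42 | 0.61 → 0.68 |
| 0.6 | −0.72 → −0.95 | 0.37 → 0.44 | 0.62 → 0.72 |

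The standard error rises. Power rises because the odds ratio conditional on Trait lies further from 1.

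**The case against.** The strongest reply is that nothing here is wrong. Randomisation makes the comparison valid, the stated power holds without the extra term, and an added covariate for a secondary outcome may be left to a statistical analysis plan that was not available for this check. All of this stands. One answer remains: section 4.3.2.2 does itself choose covariates for the parent outcomes, so extending that choice is a comment on what the protocol fixes.

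Second, State and Trait are two parts of one inventory. Adjusting one for the other does not oblige the plan to use Trait for a different instrument, and the protocol nowhere says that Trait predicts CES-D-10. This stands too. A reader might infer an internal inconsistency from the asymmetry, but the text does not support one.

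Third, week-0 CES-D-10 is the more direct covariate. A reader might infer that Trait is the best available baseline measure and that chance imbalance in parental distress passes unchecked into the estimate. The documents do not support either. A same-instrument score exists at week 0, and the adapted stress questionnaire (aRSQ-Stress) is also in the Baseline Packet. If week 0 is modelled as a response and the contrast is taken against it, stable differences between parents largely cancel. In any case chance imbalance is not bias, and the standard error already allows for it. Gender may also enter the models.

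This objection shrinks the point without removing it. No baseline CES-D-10 covariate is named. State is also measured at week 0, yet Trait is still added to its model. Section 2.5 starts the monthly questionnaires at randomisation and section 3.2 leaves participants unblinded afterwards. The protocol does not say that the week-0 form is completed before allocation is known, whereas the week -2 Trait score certainly precedes it.

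Fourth, the power figures come from a two-sample comparison of one averaged score, which section 2.6.1 itself calls conservative. They show the direction and rough size of the gain, not the power of the planned mixed model.

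**Conclusion.** This is an optional, low-cost improvement to a secondary analysis. The CES-D-10 comparison as written is valid and reaches its stated power, so it should not be read as biased or underpowered against the protocol's own target.

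For the continuous score the plan gives up some precision. With Trait as the only covariate, power would move from about 0.81 to between 0.82 and 0.93 for assumed correlations of 0.2 to 0.6. If week-0 CES-D-10 is a covariate, Trait's further contribution is about 0 to 6 points and could be nil. All these gains rest on correlations that the protocol does not give.

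A reader might extend the claim of lost precision to CES-D-10 ≥ 10. That does not hold: adjustment there increases the standard error of the log odds ratio and changes the estimand to a conditional odds ratio, with a modest gain in power.

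**What to change.** Before any comparison of parent outcomes by arm, amend section 4.3.2.2 in two respects:

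1. Extend the Trait sentence so that the Baseline Packet S-TAI-Trait score is a prespecified covariate in the CES-D-10 analyses as well as in the S-TAI-State analysis.
2. State how the week-0 CES-D-10 score enters the model. It can be a covariate if it is completed before the family knows its allocation.

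If the CES-D-10 ≥ 10 model is adjusted in the same way, report its odds ratio as conditional on the covariates. The mixed logistic model already gives a conditional odds ratio.

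The cost is one or two sentences and no new data. Each covariate uses about one degree of freedom, and parents with a missing baseline score need a simple, prespecified imputation.
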